### Procedures

#### Recruitment and enrollment

Participants are recruited from university and community-based clinics, private practices, and from the community using written and online notices/flyers. Locations for recruitment within the community using written flyers include community college campuses, bus/train stops, parking garages, public bulletin boards, public libraries, public restrooms, convenience stores, shopping centers/grocery stores with community bulletin boards, laundromats, religious centers (churches), community centers, public parks, and recreation centers. Online notices for the study are posted on Craigslist, Facebook, and Instagram. Participants are also recruited by other participants within the study. Potential participants call a private central phone number or respond to the study email address to express interest in the study. Volunteers are then screened by phone to assess basic study inclusion and exclusion criteria and to provide additional details about the study. Randomization to study condition is performed by the project coordinator following the initial phone contact (using the flip of a coin). Neither the participants nor the investigators are blinded for this trial. At the baseline/pre-intervention assessment, informed consent and additional screening assessments are administered to further evaluate and verify eligibility based on PTSD symptoms and the presence of at least one risk factor targeted by the intervention (e.g., physical inactivity, overweight status, sleep difficulties). All records are kept confidential. A list of participant names linked to their code numbers is kept in a secured file and accessed by study coordinators for project-related communications. Only code numbers are used to organize participant study data. The coded project data are kept in a separate secured file. Participant compensation consists of a $50 gift card for each of the pre-, post-, and follow-up assessment sessions, and a $10 gift card for each intervention session completed by the participant.

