## Methods

### Participants

We plan to randomize a total of 212 participants, ages 18 and over, to the two study conditions. Anticipated demographics of the overall sample, based on current data from proposed recruitment sites and prior studies recruiting from the PTSD population, are ages 37 ± 10 (mean ± SD), approximately 72% female, avg. of 12th grade education ± 3 years, and race/ethnicity composed of 64% Caucasian, 21% Hispanic-White, 10% African-American, 3% Caribbean Black, and 2% Hispanic-Non-White. Adults ages 18 and older are recruited from the community, local clinics, and via online advertisements. Criteria for inclusion are: PTSD or subthreshold PTSD [evidenced by ≥ 4 PTSD symptoms (including ≥ 1 re-experiencing symptom) endorsed as 2 or higher (moderately bothersome) on the Posttraumatic Stress Checklist (PCL-5)], the presence of at least one health risk (low physical activity, nutrition does not meet standard recommendations, overweight, sleep disruption), and ability to exercise at a moderate level. Concurrent trauma-focused psychotherapy is required through the 12-week intervention phase of the project and is provided by the project if the participant is not already receiving trauma-focused therapy in the community. On an ongoing basis, the project coordinator verifies the therapy and frequency. Although chronic illnesses are not exclusionary, medications for controlling lipids or blood pressure (e.g., beta blockers, diuretics, ACE inhibitors, statins, PCSK9 inhibitors) are exclusionary, as they would impact the lipid and blood pressure outcomes. Participants may be considered if they are able to consult with their medical provider about temporarily discontinuing these medications long enough for the medication to not be active in the system. Comorbid psychiatric conditions (e.g., depression, personality disorders, substance use disorders) are not exclusionary, as this would result in an unnaturally narrow selection of participants with PTSD. Consistent with standards for intervention studies in PTSD (Mulick and Naugle, 2010; Resick et al., 2002, 2015), those on psychopharmacological medications will be included if the regimen has been maintained as stable for ≥2 months prior to enrollment. This study is approved by the appropriate University Institutional Review Board (IRB). Written informed consent is obtained from all participants at the time of the first outcome assessment (baseline) by the laboratory research assistant(s). As with any human research, a participant may discontinue either intervention condition or any other aspect of the longitudinal study at any time, regardless of the reason.

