#### Training of study interventionists

The interventionists for the project are advanced doctoral students with experience delivering CBT-based health interventions and/or trauma-focused therapies (depending on the protocols they are trained to conduct). The health behavior interventionists are familiar with the healthy lifestyle intervention literature and develop a thorough understanding of the protocol for PTSD patients by reviewing the manual and meeting with the PI for training. Interventionists are encouraged to meet with the PI throughout intervention delivery to affirm their knowledge and confidence with the protocol and address any questions that might relate to participant-specific presentations.

For interventionists who conduct the standard trauma therapies, the PI reviews evidence-based conceptual and intervention models of trauma-focused treatment for PTSD, including Cognitive Processing Therapy (Resick et al., 2002; Resick and Schnicke, 1992), Prolonged Exposure Therapy (Foa et al., 2007; McLean and Foa, 2024), and as applicable for participants with a presentation consistent with the literature on complex-PTSD, Contextual Trauma Therapy (Gold and Quiñones, 2020). Trauma therapists are encouraged to review treatment-specific readings for the various models of treatment reviewed during training and meet with the PI and project coordinators (designated as lead interventionists) to discuss treatment options for assigned participants. Trauma therapists select treatment approaches based on the clinical presentations of participants and collaboration with participants about the various options for care. Given the literature suggesting increased rates of drop-out in exposure-based treatment, it was imperative that trauma therapists have a strong rationale for this approach, a deep understanding of its implementation, and the ability to educate the participant about the treatment delivery (Imel et al., 2013). Trauma therapists are invited to discuss their approaches to treatment, ask questions about intervention implementation and participant clinical presentations, as well as discuss relevant research on PTSD treatment during monthly research lab meetings, in one-on-one meetings with the PI, and in peer supervision meetings with the research coordinators.

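### The arm is set by the coordinator's coin flip after the first phone contact, before consent and eligibility are settled, and the sequence cannot be verified afterwards

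*Protocol article*

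**What the plan says.** The Recruitment and enrollment section fixes the method, the person and the timing: "Randomization to study condition is performed by the project coordinator following the initial phone contact (using the flip of a coin"). It continues: "Neither the participants nor the investigators are blinded for this trial".

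Consent and final eligibility follow. The same section says: "At the baseline/pre-intervention assessment, informed consent and additional screening assessments are administered to further evaluate and verify eligibility", the criteria being PTSD symptoms and at least one targeted risk factor. The Participants section agrees on timing: "Written informed consent is obtained from all participants at the time of the first outcome assessment (baseline").

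The coordinator role is not separate from the conduct of treatment. Under Training of study interventionists, trauma therapists "meet with the PI and project coordinators (designated as lead interventionists) to discuss treatment options for assigned participants". The Participants section adds: "On an ongoing basis, the project coordinator verifies the therapy and frequency".

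The target is given as: "We plan to randomize a total of 212 participants, ages 18 and over, to the two study conditions". The power summary counts 162 completers, 81 per condition. The data analysis plan relies on the randomisation for comparable groups and adds as controls any baseline comparison variables found to differ.

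**The concern.** Allocation is concealed only if nobody who can affect entry to the trial knows the arm until entry is irrevocable. Here the coordinator knows it from the flip onwards, and three things are still open: whether the person attends baseline, whether they consent, and whether they are confirmed eligible. The article describes no step that withholds the arm from the participant or from baseline staff in the meantime.

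The two conditions differ visibly. One adds twelve weekly 90-minute sessions with a $10 gift card for each. The other offers the health programme only after participation in the control arm has ended. If people learn their arm before baseline, different people may go on to enrol in each.

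A coin also leaves no list against which assignments could be checked. The trial could not show later that the recorded allocations were the ones the coin produced. At stake is whether a difference between arms can be attributed to the intervention.

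**Working it through.** **1. Order of steps, from the Recruitment and enrollment and Participants sections**

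| Step | Arm known to coordinator? | Entry settled? |
|---|---|---|
| Phone screen on basic criteria | No | No |
| Coin flip by coordinator | Yes | No |
| Attendance at baseline visit | Yes | No |
| Written consent | Yes | No |
| Verification of PTSD symptoms and at least one risk factor | Yes | Settled here |

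Three decisions fall between the flip and settled entry. If a fraction f of those allocated to one arm does not enter, and on some prognostic factor those who enter differ on average from those who do not by δ, the mean of the entrants is shifted by f × δ from that of everyone allocated. The shift cancels between arms only if f × δ is the same in both. The article gives neither f nor δ, so no figure can be put on it.

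**2. What the 212 counts.** Because the flip precedes consent, a target of 212 randomised either includes people who never consented or were found ineligible, or leaves out people who were in fact allocated. The article does not say which.

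**3. What adjustment can do.** The data analysis plan compares the arms on demographics, comorbid psychopathology, type of trauma therapy, smoking and alcohol use. Adjustment for these does not remove selection on factors outside the list, such as motivation to change health behaviour.

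**4. Chance imbalance.** Inputs: 212 randomised, 162 completers (81 per condition), alpha 0.05 (two-sided assumed), 80% power.

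*The plan's own figure.* Normal approximation: detectable d = (1.960 + 0.842) × √(1/81 + 1/81) = 0.440; with the t distribution, 0.443. The stated 0.47 is therefore conservative: 81 per arm gives 84.4% power at d = 0.47 and 88.5% at d = 0.50.

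*Fair coin, Binomial(N, 0.5).*
- N = 212: SD of one arm = √212 / 2 = 7.3; 95% range 92 to 120. P(106/106) = 5.5%; P(arms differ by 20 or more) = 19.2%; by 30 or more = 4.6%.
- N = 162: SD = √162 / 2 = 6.4; 95% range 69 to 93. P(81/81) = 6.3%.

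*Effect on power (two-sample t-test).*

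| Completers | Detectable d at 80% | Power, d = 0.47 | Power, d = 0.50 |
|---|---|---|---|
| 81/81 | 0.443 | 84.4% | 88.5% |
| 70/92 | 0.447 | 83.8% | 88.0% |
| 69/93 | 0.448 | 83.7% | 87.9% |

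Averaged over the binomial split of 162, power is 84.2% and 88.4%. The cost of not enforcing balance is 0.2 points or less on average and under 1 point at the edge of the 95% range.

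**The case against.** A fair coin is properly random and cannot be foreseen before it is tossed, so nobody can steer a person to a known next assignment as with an open list. That stands. It removes prediction before the flip but does nothing about knowledge after it.

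The article is condensed, and a dated or witnessed record of flips may exist elsewhere. That also stands: a reader might infer that the flips go unrecorded, and the text does not show this. A log would show what was reported but could not confirm it.

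The analysis plan checks and adjusts for several baseline variables, and many outcomes come from devices: automated blood pressure, the computed reactive hyperaemia and augmentation indices, point-of-care lipids and actigraphy. So it would be wrong to say that nothing downstream helps. Adjustment can expose gross imbalance, and device readings limit bias in measurement. Neither cures selection on unmeasured factors.

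A reader might also infer that flips are repeated or overridden, that the coordinator carried out the phone screen, or that coordinators have a caseload interest in the result. The documents support none of these. Screening is described without naming who does it, caseload is not mentioned, and the lead-interventionist role appears in the text on trauma therapy, which both arms receive. The coordinator does not direct the trial either; the principal investigator does.

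Finally, a reader might take unequal arms as a defect in themselves. The 81 per condition is a completer figure in the power summary, not an allocation quota, and the power cost is trivial.

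**Conclusion.** The point holds, and it should be fixed while the trial is recruiting. This is a stated rule rather than a missing detail: a study-team member allocates by coin before consent and eligibility are settled, in an open trial. That leaves a route for selection bias which the planned adjustment closes only for measured variables, and a sequence that cannot be verified afterwards. The bias cannot be sized from the article, and the article does not show that any has occurred.

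Balance is not guaranteed, but this is secondary, at under 1 point of power.

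The conclusion assumes that the flip happens between the phone contact and the baseline visit, which is the natural reading of the text. If in practice it happens after consent and confirmed eligibility, the article should say so. The objection to timing would then fall, and only the lack of independence and verifiability would remain.

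**What to change.** For participants still to be recruited:
- Use a computer-generated sequence in permuted blocks of varying size, prepared by someone not involved in recruitment or delivery. Stratification by source of trauma therapy is optional: the article says therapy "is provided by the project if the participant is not already receiving trauma-focused therapy in the community", so there are two sources. If it is used, include the stratum in the model.
- Release each allocation through a locked electronic module only after consent, eligibility confirmation and baseline assessment are recorded.

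For participants already allocated:
- Compile a log of every coin-flip allocation by arm, including people who never attended, did not consent or were found ineligible. Compare these losses between arms, and state whom the 212 counts.

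For the report:
- Describe the change of method and of timing, with its date, and run a sensitivity analysis by allocation method.

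The cost is an ethics amendment, setting up the module, and a mid-trial change in both the tool and the point of randomisation. Earlier allocations cannot be repaired, only documented.

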### Measures

#### Outcome assessment sessions

Four assessment sessions provide an indication of treatment-related outcomes. These sessions are conducted in person at a University-based laboratory at our study site in Ft. Lauderdale, FL (U.S). The first assessment (baseline) is conducted prior to the first week/study onset in each condition. The second assessment (post-treatment) is conducted at the 3-month time point (after the last healthy lifestyle session in the experimental condition). The third and fourth assessments (follow-up) are conducted at the 6-month and 12-month time points. Each assessment session consists of the same outcome measures: blood pressure, lipids, body mass index (BMI), arterial stiffness, endothelial function, heart rate variability (HRV), physical activity, nutrition, perceived stress, sleep (quantity, efficiency, quality, and restfulness), and psychological measures (PTSD symptoms, depressive symptoms). Results of the lipid measures and blood pressure are reviewed with participants following each assessment, and it is recommended to those with clinically elevated levels that they consult with their primary care physician or other medical provider about such findings.

Due to potential confounding effects on lipids and/or blood pressure, participants are asked to refrain from caffeine and strenuous exercise for 3 h, and smoking for 30 min, prior to assessment sessions. These sessions are scheduled early in the morning (approx. 8:30 a.m.) due to the requirement of fasting for lipid assessment. Non-compliance with restrictions requires rescheduling. After the lipid assessment a standardized snack (granola bar, and water/juice) is provided. A doctoral research assistant (under the direction of the PI) leads each assessment session. The data collection for the assessment sessions lasts approximately 90 min. Assessment of the following variables involving physical measurement is conducted first:

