#### Accelerometry

Participants are provided with an Actigraph wGT3X-BT watch and instructed on its use to track accelerometer-based physical activity and sleep measures each day for 1 week following each assessment session. After the watch is returned, data are downloaded for later analysis. The wGT3X-BT is the industry standard for accelerometer monitoring of physical activity and sleep (Breteler et al., 2019; Romanzini et al., 2014). The device is small (weighing only 19 grams), unobtrusive, tamper-resistant, well-tolerated, and does not hinder activity (Breteler et al., 2019). The accompanying ActiLife software is utilized for data download and analysis.

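### Allocation by coin flip follows the phone screen and precedes consent, verified eligibility and baseline measurement, so entry to the trial can depend on the arm

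*Protocol article*

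**What the plan says.** The order of events is set out in the protocol article under Recruitment and enrollment:

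1. Phone screen: "Volunteers are then screened by phone to assess basic study inclusion and exclusion criteria".
2. Allocation: "Randomization to study condition is performed by the project coordinator following the initial phone contact (using the flip of a coin").
3. Baseline visit: "At the baseline/pre-intervention assessment, informed consent and additional screening assessments are administered to further evaluate and verify eligibility based on PTSD symptoms", and also on the presence of at least one targeted risk factor.

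The Participants section confirms the timing of consent: "Written informed consent is obtained from all participants at the time of the first outcome assessment (baseline) by the laboratory research assistant(s").

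The same Recruitment section states: "Neither the participants nor the investigators are blinded for this trial". No section says that the result of the coin flip is withheld until the baseline visit.

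On baseline measurement, the section on outcome assessment sessions says: "The first assessment (baseline) is conducted prior to the first week/study onset in each condition". That ties baseline to the start of treatment, not to allocation. Under Accelerometry, the ActiGraph is used to "track accelerometer-based physical activity and sleep measures each day for 1 week following each assessment session", so baseline activity and sleep recording comes later than the visit itself.

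The Participants section gives the number: "We plan to randomize a total of 212 participants, ages 18 and over, to the two study conditions". The power summary is built on 162 completed protocols, 81 per condition. The data analysis plan takes change in the outcomes as the dependent variable, expects no baseline differences because of the randomisation, and would control for any baseline variable that turns out to differ.

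**The concern.** Randomisation makes two groups comparable at the moment of allocation. It keeps them comparable only if what happens next does not select people differently by arm. Here three filters operate after the coin flip: whether the person attends, whether the person consents, and whether eligibility is confirmed.

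The arms differ in what they ask and offer. One adds twelve weekly 90-minute sessions, with a $10 gift card for each. The other adds only the assessments, with the programme available after control participation ends. A person who knows the arm before consenting can decline for reasons tied to it. Motivation to change health behaviour is an obvious candidate, and it plausibly affects how much activity, diet and sleep change later.

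People who never consent provide no study data, so an analysis of everyone randomised is out of reach for them. Questionnaire answers and a week of worn activity and sleep recording are also values that knowledge of the arm could influence directly. Because the outcomes are analysed as changes, a distorted baseline enters the treatment contrast.

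**Working it through.** The main check is one of sequence. The arithmetic below only gives scale.

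**Sequence**

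| Step | Relation to the coin flip | Section |
|---|---|---|
| Phone screen on basic criteria | before | Recruitment and enrollment |
| Informed consent | after | Participants; Recruitment and enrollment |
| Verification of PTSD symptoms and health risk | after | Recruitment and enrollment |
| Baseline device readings and questionnaires | after (same visit as consent) | Outcome assessment sessions |
| Baseline actigraphy, 1 week | after (follows that visit) | Accelerometry |

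The two statements on the timing of consent agree, and nothing elsewhere puts allocation later.

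**Which baselines are exposed, and how**

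- Self-report (activity, nutrition, sleep, stress, PTSD and depressive symptoms) and actigraphy: through selective entry, and directly through answers or behaviour once the arm is known.
- Device-read values (lipids, BMI, endothelial function, arterial stiffness, heart rate variability): mainly through selective entry.

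**Scale of bias (illustration; b is assumed)**

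Let b be a spurious between-arm difference in the analysed outcome, in SD units, with n = 81 per arm. The shift of the test statistic is b / √(2/81), where √(2/81) = 0.157. The two-sided 5% error rate is P(Z > 1.96 − shift) + P(Z < −1.96 − shift).

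| b (SD) | Shift | Error rate |
|---|---|---|
| 0.1 | 0.64 | 9.8% |
| 0.2 | 1.27 | 24.7% |
| 0.3 | 1.91 | 48.0% |

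The article offers nothing from which b could be estimated.

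**Sample-size allowance**

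Implied total loss: 1 − 162/212 = 23.6%. The article does not split this into loss before and after baseline. With an assumed pre-baseline loss L, 212 × (1 − L) reach baseline. The share of these that must complete to give 162 is 162 / [212 × (1 − L)]. As a pessimistic case, suppose a full 23.6% is lost again after baseline. The detectable d is then for a two-sided t-test at 5% with 80% power:

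| L (assumed) | Reach baseline | Must complete for 162 | Complete after a further 23.6% loss | Detectable d |
|---|---|---|---|---|
| 10% | 191 | 85% | 146 | 0.47 |
| 20% | 170 | 96% | 130 | 0.50 |
| 30% | 148 | not attainable | 113 | 0.53 |

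For reference, 81 per arm detects d = 0.44 on the same calculation, and the plan states 0.47.

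**The case against.** Several points on the other side are fair.

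- **Some screening precedes allocation.** Basic criteria are checked by phone, so it is verification of eligibility, not all screening, that follows the coin flip. This stands.
- **Staff discretion may be small.** A reader might infer that staff who know the arm decide who is eligible. The article says investigators are unblinded, but not that the assistants running the visit are told the allocation. The PTSD checklist is a self-report measure with a fixed numeric rule. Nor does the article say when participants learn their arm. What can be said is that the coordinator knows it at once and no concealment is described, so arm-dependent entry is possible, not shown.
- **Treatment during the baseline actigraphy week.** Session 1 introduces an exercise regimen, so a reader might infer that it can overlap with baseline wear. The article states neither an overlap nor a gap, and visit scheduling is a detail that a condensed article may leave out. The inference is not supported; what is supported is that the wear week follows allocation.
- **Every baseline value is contaminated.** This goes too far for device-read measures.
- **212 cannot deliver 162.** This does not follow. The 23.6% may already include pre-baseline loss. Even with 10% lost before baseline and a further 23.6% after, the detectable effect is the planned 0.47. At 20% it only just meets the smallest planned effect of 0.50, and it misses only at 30%. The mixed model also uses all available data at each time point, so completers are not the analysed number.
- **A difference at entry need not bias change.** Suppose 10% and 25% are lost by arm, and those lost differ by 0.5 SD from those who stay. The groups then differ by (0.25 − 0.10) × 0.5 = 0.075 SD in level. A stable difference in level largely cancels in an analysis of change. Bias arises if those lost would have changed differently, which is plausible for motivation but cannot be quantified here.

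None of these points alters the stated order or the lack of any described concealment.

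**Conclusion.** The point holds as a procedural defect in the design. Allocation comes before consent, before verified eligibility and before baseline, in an unblinded trial with no described concealment. The baseline balance that the data analysis plan expects from randomisation is therefore not protected, and its remedy of controlling for variables that differ can address only what was measured.

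The conclusion rests on the sequence as stated and on the possibility that the arm becomes known before the baseline visit. It does not rest on evidence that selection has occurred. The error rates above depend wholly on assumed biases. Any effect on the sample-size allowance depends on an unstated pre-baseline loss rate and is secondary. The main concern is the validity of the between-group comparison, which later analysis cannot fully restore.

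**What to change.** **Participants still to be allocated.** Change the Recruitment and enrollment procedure to this order: phone screen, consent, verified eligibility, baseline assessment, 7-day baseline actigraphy wear, allocation, session 1. Keep the allocation unknown to staff and participants until the wear week is complete.

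**Participants already allocated by phone.** Report by arm how many were lost between coin flip and baseline, with reasons (did not attend, declined consent, found ineligible). Add a sensitivity analysis of the main between-group comparisons restricted to those allocated under the new order.

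**Cost.** An IRB amendment, allocation about a week later, and some baseline visits and ActiGraph weeks spent on people who are then not allocated. The Abstract describes the study as ongoing, so the change can protect only the remaining allocations. The sensitivity analysis will be limited by how many these are.
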